# Design of a single-arm clinical trial of regenerative therapy by periurethral injection of adipose-derived regenerative cells for male stress urinary incontinence in Japan: the ADRESU study protocol

**DOI:** 10.1186/s12894-017-0282-7

**Published:** 2017-09-25

**Keywords:** Stress urinary incontinence, Lower urinary tract symptoms, Regenerative medicine, Cell therapy, Prostatectomy, Adipose-derived regenerative cells

## Abstract

**Background:**

Male stress urinary incontinence is a prevalent condition after radical prostatectomy. While the standard recommendation for the management of urine leakage is pelvic floor muscle training, its efficacy is still unsatisfactory. Therefore, we have focused on regenerative therapy, which consists of administering a periurethral injection of autologous regenerative cells from adipose tissue, separated using the Celution® system. Based on an interim data analysis of our exploratory study, we confirmed the efficacy and acceptable safety profile of this treatment. Accordingly, we began discussions with Japanese regulatory authorities regarding the development of this therapy in Japan. The Ministry of Health, Labour and Welfare suggested that we implement a clinical trial of a new medical device based on the Pharmaceutical Affaires Act in Japan. Next, we discussed the design of this investigator-initiated clinical trial (the ADRESU study) aimed at evaluating the efficacy and safety of this therapy, in a consultation meeting with the Pharmaceuticals and Medical Device Agency.

**Methods:**

The ADRESU study is an open-label, multi-center, single-arm study involving a total of 45 male stress urinary incontinence patients with mild-to-moderate urine leakage persisting more than 1 year after prostatectomy, in spite of behavioral and pharmacological therapies. The primary endpoint is the rate of patients at 52 weeks with improvement of urine leakage volume defined as a reduction from baseline greater than 50% by 24-h pad test. Our specific hypothesis is that the primary endpoint result will be higher than a pre-specified threshold of 10%.

**Discussion:**

The ADRESU study is the first clinical trial of regenerative treatment for stress urinary incontinence by adipose-derived regenerative cells using the Celution® system based on the Japanese Pharmaceutical Affaires Act. We will evaluate the efficacy and safety in this trial to provide an adequate basis for marketing approval with the final objective of making this novel therapy widely available for Japanese patients.

**Trial registration:**

This trial was registered at the University Hospital Medical information Network Clinical Trial Registry (UMIN-CTR Unique ID: UMIN000017901; Registered July 1, 2015) and at ClinicalTrials.gov (ClinicalTrials.gov Identifier: NCT02529865; Registered August 18, 2015).

## Background

Male stress urinary incontinence (SUI) is a secondary intrinsic sphincter deficiency and a prevalent condition after radical prostatectomy [1–5]. Individuals with SUI may limit activities of daily living to reduce the chance of urine leakage; hence, SUI can have a major impact on the quality of life (QOL) of patients. The standard therapy of male SUI is pelvic floor muscle training, and clenbuterol hydrochloride, which is solely approved for SUI indication in Japan; however, the efficacy of these treatments is still unsatisfactory. Another potential therapy is periurethral injection of collagen, but its efficacy has only been shown in short-term trials [6, 7], and this treatment is not currently approved for SUI in Japan. Another potential alternative involves the implantation of an artificial urinary sphincter, which is recommended for patients with severe incontinence [8–10]. Unfortunately, according to a Japanese report from the Office of Pharmaceutical Industry Research (OPIR News No.45), new pharmaceutical agents for SUI have not been developed in Japan as of 2015.

Meanwhile, we have focused on regenerative cell therapy of urethral sphincter deficiency based on several experimental studies [11–16]. We previously confirmed that periurethral injection of cultured adipose-derived stem cells improved leak point pressure in an SUI animal model [17]. Therefore, we planned a preliminary clinical study with the objective of developing a novel treatment using autologous adipose-derived regenerative cells (ADRCs) without cell culture. In other words, the ADRCs are isolated in a few hours by the Celution® system (Cytori Therapeutics, Inc., San Diego, CA, USA). That study was approved by the Ethics Committee of the Nagoya University Graduate School of Medicine, and also by the committee of the Japanese Ministry of Health, Labour and Welfare (MHLW) according to the Guidelines on Clinical Research using Human Stem Cells [18], and registered at the University Hospital Medical information Network Clinical Trial Registry (UMIN-CTR Unique ID: UMIN000006116). Based on an interim data analysis of that exploratory clinical study, we obtained preliminary evidence confirming that the periurethral injection of isolated ADRCs is effective and safe for use in the male SUI patients [19, 20]. However, the Celution® system is not currently available for treatment purposes in Japan. This system is only currently approved for use in clinical research under the Japanese ‘Act on the Safety of Regenerative Medicine’. Therefore, as our objective is to disseminate this novel therapy throughout Japan as soon as possible, we prepared a confirmatory study protocol and began discussions with the Japanese regulatory authorities to build a bridge from ‘benchside to bedside to community’ in cooperation with Cytori Therapeutics, Inc.

In this article, we provide the detailed design of this investigator-initiated clinical trial in male SUI patients as a pivotal study for the licensure of this therapy in Japan (the ADRESU study). Incidentally, the main design of this trial is undergoing the process of approval by the Pharmaceuticals and Medical Device Agency (PMDA), which is responsible for reviewing new pharmaceuticals, medical devices, and regenerative medicines; however, whether the final approval by PMDA is granted or not will depend on the data obtained in this study.

## Methods/Design

### Overall design and objective

The primary objective of this trial is to evaluate the efficacy and safety of periurethral injection of autologous ADRCs separated with the Celution® system in male SUI patients. The ADRESU study is an open-label, multi-center, single-arm study involving a total of 45 male patients with stress urinary incontinence, with mild-to-moderate urine leakage persisting more than 1 year after prostatectomy that achieved insufficient symptom improvement by behavioral and pharmacologic therapies. The primary endpoint of this study is the rate of patients with improvement in urine leakage volume. Our specific hypothesis is that the rate of patients with improvement in urine leakage volume, defined as a reduction greater than 50% from baseline by 24-h pad test, is higher than a pre-specified threshold of 10%. Additionally, we will consider whether or not patients with symptom improvement will also show improvement in QOL scores.

### Selection of subjects

First, we decided to select male patients with SUI as our patient population, not only because urinary incontinence mechanisms differ by sex, but also because few female data were available in our former study. Next, we considered prior incontinence history, in other words, duration and severity of incontinence after surgery. Regarding the duration of incontinence, there is enough evidence to show that patients who develop post-prostatectomy incontinence persisting for a period longer than 1 year are unlikely to recover function thereafter [1–5]. With respect to incontinence severity, we restricted our population to patients with mild-to-moderate urinary incontinence based on subgroup analysis of our available data in comparison with more severe patients. The mean reduction rate of leakage volume at 12 months of patients with mild-to-moderate and severe urinary incontinence was 62.6% and 18.0%, respectively (Table 1).

**Table 1 Tab1:** Reduction rate of urine leakage volume from baseline by 24-h pad test in exploratory study

	Daily urine leakage volume at baseline	Reduction rate of daily urine leakage volume			
		1 month	3 months	6 months	12 months
Severe SUI (*n* = 5)	531.1 ± 229.2 g	−40.0 ± 62.6%	−6.2 ± 56.2%	2.9 ± 58.3%	18.0 ± 46.9%
Mild-to-moderate SUI (*n* = 9)	85.2 ± 55.0 g	17.0 ± 66.1%	32.2 ± 54.7%	27.6 ± 50.5%	62.6 ± 19.0%

Each data point represents the mean ± SD

The detailed inclusion criteria are as follows:Males with stress urinary incontinence persisting more than 1 year after either of the following surgical procedures, with insufficient improvement of symptoms by behavioral and pharmacological therapies:i.Patients with symptoms after radical prostatectomy for localized prostate cancer and currently without relapse/metastasis, and prostate specific antigen (PSA) level less than 0.1 ng/mL for over 1 yearii.Patients with symptoms after transurethral prostatectomy or laser prostatectomy for prostatic hyperplasia and PSA level less than 4.0 ng/mL over 1 year
Age of 20 years or aboveMild-to-moderate urinary incontinence by the 24-h pad testPatients who can keep a bladder diary in a satisfactory mannerPatients that can provide a signed informed consent

The main exclusion criteria are as follows:Concurrent with any other types of urinary incontinenceHistory of urinary or reproductive surgery within 6 monthsHistory of behavioral therapy or pharmacotherapy initiation within 3 monthsConcurrent with diabetes insipidusHistory of radiotherapy in the lower urinary tractHistory of ADRCs treatment for stress urinary incontinenceHistory of any type of cell therapy within 6 monthsParticipation in any other clinical trial within 3 monthsConcurrent with lower urinary tract obstructionConcurrent with urolithiasis, urinary tract infection or interstitial cystitisHistory of recurrent urinary tract infectionHistory or suspicion of malignant neoplasm within the last 5 yearsAny other patients whom the trial investigator deems ineligible for this study

### Selection of patients for the control group

In general, a concurrent control group is needed for a clinical trial as the most common clinical trial designs for a confirmatory trial is a randomized, controlled, parallel-group design [21, 22]. Potential candidates for the control group include those receiving approved treatment (pharmaceuticals, behavioral therapy, or surgical procedure), placebo, sham treatment, or no treatment.

Regarding approved treatments, as shown in ‘*Selection of subjects*’, there is no conventional therapy in Japan for patients eligible for this study. To select placebo or sham treatment as a control group is not acceptable for clinical and ethical reasons given the invasive nature of the periurethral injection and liposuction. While a no-treatment group may be effective as a potential comparator, such a comparison is not always necessary because patients with post-prostatectomy incontinence persisting for 1 year are unlikely to improve from 1 year onward [1–5]. Therefore, we decided to implement a confirmatory single-arm study.

### Registration and informed consent

Patients are registered temporarily as candidates for this study after providing written informed consent and the investigators have confirmed that they meet most of the eligibility criteria. Thereafter, an investigator reviews the patient’s urination diary, the method of data collection, that is that the patient measures the weight of the urination pad, the number of incontinence episodes, and the number of pads used, and then records it at home for 7 consecutive days. Then, these data are assessed to determine eligibility by the inclusion criteria no. 3. After all eligibility criteria are confirmed, the patients are enrolled via electronic data capture system (Viedoc™, PCG Solutions Ab. Uppsala, Sweden), with the subsequent initialization of the treatment process.

### Preparation and injection of ADRCs

About 250 to 300 mL and an additional 20 to 30 mL of adipose tissue are manually suctioned from subcutaneous layer in abdominal wall or hip under general or spinal anesthesia. About 250 to 300 mL of extracted adipose tissue are applied into the Celution® system. This system is an apparatus designed to isolate ADRCs from human suctioned fat semi-automatically in 1 to 2 h. Collected ADRCs by the Celution® system are composed of a heterogeneous cell population, including adipose-derived stem cells, endothelial (progenitor) cells and vascular smooth muscle cells [23]. Finally, we will obtain a 5-mL ADRCs solution including about 1 × 10^7^ nucleated cells.

For periurethral injection, we will prepare two materials: one consists of 1 mL of ADRCs solution for direct injection into the sphincter, and the other is a 20 mL mixture comprising 4 mL of ADRCs solution with 16 mL of fat for injection into the submucosal spaces. A ‘NUU Device’™ (Hakko Co. Ltd. Bunkyo-ku, Tokyo, Japan), which is a puncture needle of 38 cm in length, is inserted through the endoscope into the urethra under direct endoscopic vision. Initially, 1 mL of ADRC solution are injected using the 22 G puncture needle to a 5- to 10-mm depth into the rhabdosphincter at 5 and 7 o’clock positions. Subsequently, a 20-mL mixture of ADRCs and fat is administered with an 18 G puncture needle to about a 10-mm depth into the submucosal spaces at the 4 and 8 o’clock positions (if needed 6 o’clock position) at the external urethral sphincter area. Detailed procedures for the preparation and injection of ADRC solutions are provided in previous reports [19, 20].

### Response variables (outcomes)

Patients will be followed-up for 52 weeks after injection of ADRCs. The ADRESU study schedule is shown in Table 2.

**Table 2 Tab2:** The ADRESU study data collection schedule

	Screening period		Operation	Observation period							
	Provisional registration	Registration	Day 0	Day 1	At end of hospitalization	Week 2	Week 4	Week 12	Week 26	Week 38	Week 52
Eligibility criteria	X	X									
Vital signs^a^			X	X	X	X					
Oxygen saturation			X	X	X	X					
Laboratory tests											
Infections^b^		X									
Hematology^c^, Biochemistry^d^, CRP, Coagulation^e^, Urinalysis^f^		X		X	X	X	X	X	X		X
PSA		X						X	X		X
12 Lead electrocardiography		X		X	X	X					
Chest X-rays		X									
Urination diary^g^		X				X	X	X	X	X	X
QOL scores^h^		X							X		X
Patient overall satisfaction		X							X		X
Urodynamic parameters^i^		X				X	X	X	X		X
Transrectal ultrasonography		X						X	X		X
MRI		X				X			X		X
Liposuction			X								
Periurethral injection of ADRCs, and mixture of ADRCs and fat			X								
Concomitant therapies	X	X	X	X	X	X	X	X	X	X	X
Adverse events	X	X	X	X	X	X	X	X	X	X	X

^a^ Blood pressure, pulse rate, body temperature

^b^ HBs antigen, HCV antibody, HIV antibody, serologic test of syphilis

^c^ Red blood, hemoglobin, hematocrit, white blood cell count, fraction of leucocytes (basophil, eosinophil, neutrophil, lymphocyte, monocyte), platelet count

^d^ Total protein, albumin, total cholesterol, blood urea nitrogen, creatinine, uric acid, sodium, chloride, potassium, calcium, phosphate, lactate dehydrogenase, aspartate aminotransferase, alanine aminotransferase, alkaline phosphatase, gamma-glutamyl transferase, total bilirubin, creatinine kinase

^e^ Prothrombin time, activated partial thromboplastin time, fibrinogen

^f^ pH, protein, glucose, urobilinogen, occult blood

^g^ Urine leakage volume, number of incontinence episodes, number of pads used

^h^ International Consultation on Incontinence Questionnaire-Short Form, King’s Health Questionnaire

^i^ Maximum urethral closing pressure, functional profile length, abdominal leak point pressure

*Abbreviations: CRP* C-reactive protein, *PSA* Prostate-Specific Antigen, *QOL* quality of life, *MRI* magnetic resonance imaging, *ADRCs* adipose-derived regenerative cells

As a general rule, the primary endpoint should reflect clinically relevant and meaningful effects [24]. The USA Food and Drug Administration (FDA), which is the regulatory authority of the USA, recommends commonly used effectiveness endpoints for SUI listed as follows: amount of urine leakage (1-h pad weight test, 24-h pad test), number of incontinence episodes, number of pads used, QOL, and urodynamic measurements [25]. However, the FDA insists that dryness is the ultimate goal of treatment for SUI. The FDA also recognizes that many patients are satisfied even if they only experience a reduction in urine leakage. Accordingly, the FDA recommends defining the clinically meaningful level as improvement in pad weight or improvement in the number of incontinence episodes defined as a reduction from baseline greater than 50%. Based on interim data of improvement in pad weight in the exploratory study, we selected the rate of patients with improvement in urine leakage volume (defined as reduction from baseline greater than 50% by 24-h pad test) at 52 weeks (last observation carried forward) as the primary endpoint of the ADRESU study.

The secondary endpoints are as follows:Rate of patients at each evaluation time point with reduction in urine leakage volume greater than 50% from baseline by 24-h pad testUrine leakage volume at each evaluation time point by 24-h pad testRate of patients at each evaluation time point with a reduction greater than 50% from baseline in the number of incontinence episodes per dayNumber of incontinence episodes per day at each evaluation time pointNumber of pads used per day at each evaluation time pointQOL score (International Consultation on Incontinence Questionnaire-Short Form [ICIQ-SF] and King’s Health Questionnaire [KHQ]) at each evaluation time pointOverall patient satisfaction at each evaluation time pointUrodynamic parameters (maximum urethral closing pressure, functional profile length, and abdominal leak point pressure) at each evaluation time pointBlood flow at the injection site measured by transrectal enhanced ultrasonography at each evaluation time pointInjection site evaluated by pelvic magnetic resonance imaging (MRI) scan at each evaluation time point

We also plan confirm the improvement tendency on QOL scores in SUI patients who satisfy the primary endpoint (defined as ‘Responders’), that is, that a point estimation of reduction rate on ICIQ-SF score is greater than 0%.

### Number of subjects

Our specific hypothesis is that the rate of ‘Responders’ as a primary endpoint, is higher than a pre-specified threshold of 10% given the poor likelihood of natural recovery of incontinence in these subjects [1–5]. Conservatively, the expected effectiveness rate is 30% because the rate of ‘Responders’ on interim analysis is 33.3% at 6 months and 66.7% at 12 months. Using two-side testing at a 5% significant level, we estimated that a sample of 41 patients was needed to achieve a 90% power of detection based on statistical calculations. Accordingly, a sample size of 45 patients was set in the ADRESU study anticipating a 10% loss to follow-up.

### Statistical analysis

Analysis of this trial is based on an intention to treat principle. The primary analysis is performed in the Full Analysis Set that consists of all the enrolled subjects who injected ADRCs. The rate of ‘Responders’ for the primary endpoint and the secondary endpoints of 1) and 3) were estimated and their 95% confidence intervals are calculated using the Clopper-Pearson method. The descriptive statistics (e.g., mean, standard deviation, minimum, median, and maximum) of the secondary endpoints of 2) and 4)-10) are provided at each evaluation time point.

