### Ethics approval and current status on this trial

This study protocol is in accordance with the Declaration of Helsinki [26] and the Pharmaceutical Affaires Act in Japan. The protocol of this trial was approved by the following Institutional Review Boards: Nagoya University Hospital (No. 272001), Kanazawa University Hospital (No. 9009), Shinshu University Hospital (No. 1483), and Dokkyo Medical University Hospital (No. S-288). In June 2015, a clinical trial notification as a new medical device, much like a U.S. Investigational Device Exemption application, was accepted by the MHLW. The first patient completed the provisional registration in August 20, 2015 and received transplantation of ADRCs in September 1, 2015. The ADRESU study has currently enrolled 33 patients and is still recruiting patients from the four institutes (Nagoya University Hospital, Kanazawa University Hospital, Dokkyo Medical University Hospital, and Shinshu University Hospital). We are planning to enroll 45 patients as the full analysis set. The limit of enrollment will be December 2017, and the planned study end is March 2019.

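### The primary analysis set is described as intention to treat but contains only injected patients, so enrolled patients whose harvest or cell separation ends without injection leave the denominator

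*Protocol article*

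**What the plan says.** The Statistical analysis section opens with the principle: "Analysis of this trial is based on an intention to treat principle". Its next sentence defines the primary population: "The primary analysis is performed in the Full Analysis Set that consists of all the enrolled subjects who injected ADRCs".

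The order of events is given elsewhere in the article:

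- **Registration and informed consent:** "After all eligibility criteria are confirmed, the patients are enrolled via electronic data capture system", and this happens "with the subsequent initialization of the treatment process". Enrolment therefore precedes every treatment step.
- **Preparation and injection of ADRCs:** 250 to 300 mL of fat for the device, plus a further 20 to 30 mL, "are manually suctioned from subcutaneous layer in abdominal wall or hip under general or spinal anesthesia". The fat then goes into the Celution system: "This system is an apparatus designed to isolate ADRCs from human suctioned fat semi-automatically in 1 to 2 h". Injection follows.
- **Table 2:** liposuction and injection are both on Day 0, after Registration.

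On numbers, the section Number of subjects derives 41 patients and raises this to 45 for 10% loss to follow-up. The section on ethics approval and current status says: "We are planning to enroll 45 patients as the full analysis set".

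**The concern.** The principle and the set do not match. Intention to treat keeps every enrolled patient in the analysis; the set as defined keeps only those who reached the last step of the procedure. Anesthesia, liposuction and one to two hours of device processing lie between enrolment and injection. A patient whose harvest is inadequate, whose separation run gives nothing to inject, or whose procedure is stopped, is enrolled but not counted.

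This matters more here than in many single-arm trials. The objective concerns cells separated with the Celution system, the clinical trial notification is for a new medical device, and the study is meant to be pivotal for licensure. A separation that yields nothing to inject is a failure of the tested procedure. There is no control arm, so the efficacy claim rests on one responder rate compared with 10%. If that rate depends on the procedure having been completed, it overstates what a patient entering treatment can expect.

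**Working it through.** **Inputs.** Threshold 10%, expected rate 30%, two-sided 5%, 90% power, n = 41 raised to 45 (Number of subjects); Clopper-Pearson 95% interval (Statistical analysis). The article gives no number of enrolled but uninjected patients. I call it k and assume k = 0 to 5, each counted as a non-responder. I take success to mean a lower 95% limit above 10%, which is the exact binomial test with at most 2.5% in the upper tail.

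**1. The plan's own figure.** The critical count c is the smallest c with P(X ≥ c | n, 0.10) ≤ 0.025, and power is P(X ≥ c | n, 0.30). For n = 41, c = 9, the upper tail is 1.81% and power is 90.6%. For n = 40, c = 9 and power is 88.9%. So 41 is the smallest n reaching 90% and is reproduced. The allowance for loss gives 41/0.9 = 45.6, close to the stated 45. The sample size is not at issue.

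**2. Reading A: 45 enrolled in total, 45 − k injected.** Over all enrolled, success needs at least 10 of 45. Response among the injected is 30%.

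| k | Injected | Count needed, injected set | Power, injected set | Power, all 45 enrolled |
|---|---|---|---|---|
| 0 | 45 | 10 | 90.7% | 90.7% |
| 1 | 44 | 10 | 89.1% | 89.1% |
| 2 | 43 | 9 | 93.3% | 87.3% |
| 3 | 42 | 9 | 92.0% | 85.2% |
| 4 | 41 | 9 | 90.6% | 83.0% |
| 5 | 40 | 9 | 88.9% | 80.4% |

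The two sets disagree only for k = 2 to 5, and only with exactly 9 responders. For k = 2 the lower limit is 10.04% for 9/43 (success) and 9.58% for 9/45 (no success). The chance of such a disagreement is the difference between the last two columns: 93.3 − 87.3 = 6.0 percentage points at k = 2, rising to 88.9 − 80.4 = 8.5 at k = 5.

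Expressed as a rate: with a 5% pre-injection failure rate the expected all-enrolled response is 0.30 × 0.95 = 28.5%, and power at 45 enrolled falls from 90.7% to 86.5%. With 10% it is 0.30 × 0.90 = 27%, and power is 81.2%. Both failure rates are assumptions.

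**3. Reading B: 45 injected, 45 + k enrolled.** The critical count is 10 at every size from 45 to 50, so the verdict does not change.

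| Responders / enrolled | Estimate | Lower 95% limit |
|---|---|---|
| 10/45 | 22.2% | 11.2% |
| 10/47 | 21.3% | 10.7% |
| 10/48 | 20.8% | 10.5% |
| 10/50 | 20.0% | 10.03% |

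The margin nearly disappears only at this smallest passing count. Near the planned 30% it remains wide: 14/45 has a lower limit of 18.2% and 14/50 has 16.2%.

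**The case against.** The strongest reply is that treated-patient sets are common in single-arm trials, and that the stated objective is about the injection, so a set anchored on injection fits it. Liposuction and injection fall on the same day and separation takes one to two hours, so the window for loss during the procedure is short. The article reports no failed harvest, failed separation or abandoned procedure. All of this stands. It limits the likely size of the problem and would support a treated set that is named as such. It does not reconcile two adjacent sentences, one of which claims intention to treat.

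Three stronger readings are tempting, and the article does not support them:

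- **That harms in uninjected patients go uncounted.** The section ties this set only to the primary analysis, and Table 2 collects adverse events from provisional registration onward. A safety population that a condensed article does not describe is not a defect.
- **That uninjected patients are replaced.** The sentence on enrolling 45 as the full analysis set fits equally well with expecting every enrolled patient to be injected. No replacement rule is stated.
- **That every failure of the separation step is removed.** A low cell yield that is still injected stays in the set. Only runs that end without injection leave it.

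A set of all patients in whom liposuction was started would not answer the point fully either, because it still omits enrolled patients who never reach surgery.

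**Conclusion.** The point holds as a contradiction between the stated principle and the stated primary set, with a bias that can only favour the treatment. Its size is unknown and is zero if every enrolled patient is injected. If 45 is the total enrolled, two to five uninjected patients can turn a failed trial into a successful one, but only at exactly 9 responders. If 45 is the number injected and up to five more are enrolled, the verdict is unaffected and only the estimate falls, by 22.2 − 20.0 = 2.2 percentage points at 10 responders with five uninjected. The article does not say which meaning of 45 applies. These results assume success is judged by the lower Clopper-Pearson limit against 10% and that uninjected patients count as non-responders. The change is worth making before analysis; it does not put the sample size or the design in doubt.

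**What to change.** In Statistical analysis, make the primary analysis one of all enrolled patients, with those not injected counted as non-responders, which is what the stated principle implies. Keep the injected-only set as a supportive analysis.

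If the injected set is to remain primary, the minimum is to call it a treated (modified) set, remove the intention-to-treat label from it, add the all-enrolled analysis as a sensitivity analysis, and report the number of uninjected patients with reasons.

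In Number of subjects and in the section on current status, state whether 45 means enrolled or injected.

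The cost is a wording change in the protocol and analysis plan, plus a count of uninjected patients with reasons. The article reports 33 patients enrolled and recruitment continuing, so the change could precede the final analysis. The downside is that the reported responder rate may be slightly lower. If 45 is the total enrolled, power also falls as in the first table.
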